### Procedure

Participant eligibility will be assessed by the researcher based on the inclusion and exclusion criteria (Table 1) at an initial screening visit. Participants will also be asked to complete the Physical Activity Readiness Questionnaire (PARQ) [21] in order to identify any potential contraindications to increasing their physical activity levels. If participants score positively, they will be advised to consult their doctor about whether they should participate in the study.

After obtaining informed consent, the researcher will arrange a visit to collect baseline outcome measures. Participants’ level of intellectual disability will be assessed with questions assessing an individual’s level of ability and need for support in five key areas of functioning: eating and drinking, intimate care, personal safety, communication and decision making. A total score (range 5–25) is obtained by adding together the scores from the five individual questions. This will be used to categorise the level of intellectual disability as mild, moderate, severe or profound. The cut-offs corresponding to the four categories of intellectual disabilities were derived in a previous study [22] and shown to have a good level of agreement with a validated structured assessment of functioning and ability level, the Vineland’s Adaptive Behaviour Scale [23]. Participants will then be randomised into the TAKE 5 intervention or WWToo intervention. The researcher will telephone an interactive voice response system (IVRS), hosted by the Robertson Centre for Biostatistics, University of Glasgow. The researcher will register each participant in the study, by giving the participants’ cluster number, the number of individuals within the cluster, level of intellectual disabilities and presence of Down Syndrome. After registering each participant, the system will notify the principal investigator of the allocation (TAKE 5 intervention or WWToo intervention). During post randomisation, participants will be contacted by the research dietitian delivering the interventions and arrangements will be made for their first session. Intervention sessions will take place in a participant’s own home or, if an individual prefers, in out-patient facilities located in the local learning disabilities team base, or other NHS Greater Glasgow & Clyde setting. The researcher collecting the data will be blind to group allocation. After the first 6 months of weight loss phase and at 12 months, all outcome measures will be repeated. These data will be used to determine whether any changes in outcome measures have been maintained.

### Interventions

Both interventions will be delivered by a research dietitian. The session frequency (9–12 sessions in the weight loss phase and six sessions in the weight maintenance phase) is to allow appointments to be organised flexibly to maximise the consistent involvement of family and paid carers. Previous research has shown that the involvement of family and paid carers contributes to the effectiveness of weight management interventions for adults with intellectual disabilities [24, 25]. Each session will last approximately 40–60 min duration. This is to allow some flexibility in the session content, required to take account of the individual needs and abilities of participants. For example, some participants and carers may prefer to have shorter sessions or have extra sessions to develop an understanding of the information. This study will use appropriate methods and techniques for augmentative communication, e.g. talking mats and pictorial explanations that aim to enable participants to express their choices during the intervention [26]. Accessible resources, appropriate to the developmental levels of adults with intellectual disabilities were developed during the TAKE 5 feasibility study and will be used to support participants in both intervention arms. Supporting resources are designed to be used flexibly with adults with all levels of learning disabilities, involving family and paid carers where appropriate.

#### TAKE 5

TAKE 5 is an individualised intervention involving family or paid carers to support participants, where appropriate. It was adapted specifically for use with adults with intellectual disabilities in that it is designed to be delivered on a one-to-one basis with support from carers in the individual’s home environment instead of a group setting as in the GCWMS intervention [13].

#### TAKE 5 intervention components

The main themes discussed at each session for weight loss and weight maintenance are illustrated in Tables 2 and 3, respectively. Each session will focus on a discussion point on diet and physical activity and incorporate behavioural change techniques (Table 2).

**Table 2 Tab2:** **Intervention key themes underpinning weight loss sessions**

Session	TAKE 5	Waist Winners Too
1	Benefits of losing weight and motivation towards a healthy lifestyle	Introduction to health and weight
2	Introduction to individualised energy deficit diet and the importance of physical activity	Planning meals
3	Principles of healthy eating and improving physical activity levels	Food labelling and fats
	Introduction to physical activity diaries and pedometer	
4	Healthy ways to cook, meal planning and shopping lists	Food labelling salt and sugar
	Emotions and overeating	
5	Disadvantages of eating out and take-aways	Shopping, budgeting, snacks, eating out and take-aways
	Using behaviour change to alter ‘bad habits’	
6	Coping with cravings and evaluating knowledge of physical activity	Alcohol and other drinks
7	Diet myths and introduction to new ways to motivate participation in physical activity	Benefits of exercise
8	Relapse prevention	Review
9	Evaluate success up to now	What have we learned

**Table 3 Tab3:** **TAKE 5 key themes underpinning weight maintenance sessions**

Session	Theme
1	Weight maintenance and new individualised maintenance dietary plan
2	Importance of being active and adopting regular eating patterns
3	Regular self-monitoring of weight and food intakes
4	Overview of barriers to healthy eating and physical activity
5	Snacking, lapses, eating out/social activities
6	Healthy menu plan and review of principles of weight maintenance

### Diet

#### Phase 1—weight loss

To achieve a healthy sustainable weight loss of 0.5–1.0 kg per week, a daily EDD of 600 kcal is recommended [11, 12]. Each individual’s daily energy deficit will be calculated based on the estimate of their total energy expenditure −2,510 kJ (600 kcal). Basal metabolic rate (BMR) will be calculated with gender, age, height and weight using the Mifflin St. Jeor equation [27]. Total energy expenditure is estimated from BMR multiplied by a physical activity level of 1.3 [28].

The EDD provides daily caloric intake from a specified number of daily portions from the five food groups in the *Eatwell* plate: starchy foods such as bread, rice, potatoes and pasta; meat/fish and alternatives; fruit and vegetables; milk and dairy products; foods high in sugar and fat [29]. The EDD also gives specific advice on portion sizes and alternatives to energy dense food stuffs.

#### Phase 2—weight maintenance

In the weight maintenance phase, dietary intake will continue to be based on the principles of portions from the five food groups from the *Eatwell* plate [29]. However, this will not incorporate a daily EDD approach to include a deduction of 600 kcal. Instead, each individual’s energy requirements will be calculated to maintain energy balance.

### Physical activity

#### Phase 1—weight loss

Results from the single-stranded feasibility study of TAKE 5 reported that individuals with intellectual disabilities and obesity have very sedentary lifestyles and have low levels of physical activity spending an average of 13.1 (SD 16.2) min per day in moderate-to-vigorous-intensity physical activity [15]. The majority of physical activity recommendations advocate 30 min of moderate-to-vigorous physical activity on most days of the week [30, 31]. This may be unrealistic and unattainable for some individuals with intellectual disabilities. Therefore, consensus guidelines on physical interventions for beginners [32] will be adhered to, initially aiming to support participants to progressively increase regular participation in physical activity and reduce time spent being sedentary.

In each session, physical activity goals will be negotiated and set based on the individual’s current level of physical activity, physical ability and individual’s expressed preference, with the overall aim to gradually work towards current physical activity recommendations advocated for all adults.

Participants will be encouraged to reduce the time spent sedentary, i.e. watching TV, by accumulating bouts of physical activity over the course of the day. Current activity across three types of physical activity will be reviewed with each participant and carer:

Activity at home as a replacement for sedentary behaviour, e.g. housework and gardeningWalking—based on baseline average steps per day, individuals will be encouraged to set targets to progressively increase walking behaviour and use pedometers to monitor step countsSport and exercise—information will be given to each participant on local leisure facilities and clubs with disability accessible sports and exercise groups/classes.

#### Phase 2—weight maintenance

The importance of physical activity will be highlighted in the maintenance phase as it plays an important role in sustaining any reductions in body weight [12, 13]. Individuals will be encouraged to build on the levels of physical activity they achieved in phase 1 and continue to aim to meet clinical recommendations.

### Behaviour change techniques

#### Phase 1—weight loss

It is recommended that behaviour change techniques are incorporated into weight management interventions to support and maintain changes in attitudes and behaviour in relation to healthy lifestyle patterns such as healthy eating, increased physical activity and a decrease in sedentary behaviour [12, 13]. The techniques incorporated into the TAKE 5 intervention are based on the recommendation of clinical guidelines and will include self-monitoring, goal setting, management of eating behaviours, relapse prevention, stimulus control, cue avoidance, reinforcement and social assertion [15, 18]. There are recognised challenges to supporting behaviour change in adults with intellectual disabilities. Therefore, TAKE 5 uses support from family or paid carers to provide encouragement and motivation for behaviour change and the behavioural methods above flexibly in keeping with the needs and ability of levels of participants [33].

Goal setting and dietary self-monitoring are key aspects of behaviour change [13]. Short-term goals incorporating dietary change and physical activity will be set by participants at the end of each session and reviewed subsequently. Participants and carers will be provided with daily diaries to facilitate monitoring of dietary intakes and level of participation in physical activity. These will be reviewed at each session and used to monitor progress towards goals, identify potential barriers to change and discuss means to achieve goals. This information is used as part of the intervention and will not be used as a source of data for formal statistical analyses. When an individual’s level of abilities allows additional behavioural change, techniques will be included within the TAKE 5 intervention, such as problem solving and assertiveness.

#### Phase 2—weight maintenance

To maintain a healthy body weight, behavioural strategies used in the weight loss phase will continue to be used flexibly. Specific approaches, such as problem solving and lapse and relapse prevention, are particularly relevant to discuss and use during maintenance sessions. Participants will be encouraged with support from carers where appropriate to maintain the healthy lifestyle habits from phase 1. Furthermore, they will be encouraged to regularly self-monitor their body weight, food intake and habitual physical activity. Goal setting will be used at the end of each session (Table 3).

#### Control intervention (WWToo)

WWToo is a health education intervention developed by a partnership group consisting of NHS dietitians, intellectual disability nurses, health improvement specialists and representatives from Glasgow Life, responsible for delivering community leisure facilities. WWToo was adapted from a mainstream Waistwinners programme into an accessible format for adults with intellectual disabilities. The Waistwinners programme aims to increase knowledge and skills to improve behaviour related lifestyle habits such as healthy eating, weight management and physical activity. The programme is a group-based intervention delivered over eight weekly sessions.

For the purpose of this research study, the delivery of the WWToo intervention has been modified to an intervention delivered on a one-to-one basis. Participants in this control intervention will receive the same number of face-to face sessions as participants in the TAKE 5 intervention. To retain participants to the study for the same duration as TAKE 5, a weight maintenance phase to WWToo was developed.

### WWToo intervention components

#### Phase 1—weight loss

##### Diet

Dietary change will be based on non-quantitative advice based on the food groups from the *Eatwell* plate [29]. Participants will not be given quantitative dietary advice but will be provided with knowledge about healthy and unhealthy food groups to assist them to make an informed decision on optimal food choice.

#### Physical activity

The physical activity component will follow the same guidelines set out for the participants in the TAKE 5 intervention. However, participants will not be encouraged to self-monitor or increase their daily step counts using a pedometer.

#### Behaviour change techniques

The behaviour change technique goal setting and self-monitoring will be incorporated into the intervention purely with respect to dietary targets and physical activity. Participants will be invited to set a general dietary or a physical activity goal for each session and to self-monitor their food intake and physical activity.

#### Phase 2—weight maintenance

At each session, the dietitian will weigh the participant and discuss their weight in the context of sustaining any weight change. The opportunity for participants or carers to ask any questions relevant to diet and physical activity will be available at every session.

### Outcome measures

A researcher (LH) who is blind to study group allocation is responsible for collecting all outcome measures. Demographic, health questionnaires and all other outcome measures will be completed at baseline, at 6 months and at 12 months.

#### Primary outcome

The primary outcome measure will be the mean difference in body weight (kilograms (kg)) at 12 months from baseline between the two treatment groups.

#### Secondary outcome

Secondary outcomes include weight loss of 5% or more of initial body weight, change in BMI, waist circumference and percentage body fat. Mean percentage time per day spent engaged in moderate-vigorous intensity physical activity, light intensity physical activity and engagement in sedentary behaviour.

#### Anthropometric outcomes

Participants will be invited to have their weight, height, waist circumference and triceps skinfold thickness measured. Measurements will be made with the participant wearing light clothes without shoes. All measurements will be made in duplicate and the final value calculated as the mean of the two measurements. Weight in kilograms will be measured to the nearest 100 grams (g), using SECA877 scales (SE approval class III; SEA Germany). Height in metres (m) will be measured to the nearest 1 mm using the SECA Leicester stadiometer (SECA, Germany). The height (m) and weight (kg) will be used to calculate BMI using the formula BMI = weight/height (kg/m^2^).

Waist circumference will be measured to the nearest 0.5 cm at the midpoint between the iliac crest and the lowest rib, in full expiration whilst the participant is standing [34].

Due to the invasive nature of skinfold measurements and the issue of level of compliance of adults with intellectual disabilities, percentage body fat will be calculated using only the triceps skinfold thickness (mm) measured to the nearest 1 mm, waist circumference (cm) and age (years) of the participant. Separate regression equations for male and female participants, developed by Lean et al. [35] will be used to predict body density and percentage body fat.

#### Physical activity outcome

To objectively measure physical activity, all participants will be invited to wear accelerometers for 7 days on three occasions, at baseline, 6 and 12 months. Accelerometers have been used in studies involving adults with intellectual disabilities and shown to be well utilised by this group and to be a reliable and effective measure of levels of physical activity [36, 37].

Actigraph GT3X+ accelerometers (Manufacturing Technology Inc., Florida) will be worn at the hip, attached to a belt worn round the waist. Participants will be invited to wear the actigraph GT3X+ over a 7-day period. Instructions will be given to wear the actigraph during all waking hours, except when showering, bathing or swimming.

In keeping with guidelines on the validity of accelerometer data, the minimum data requirement will be set at 6 h of data, on at least 3 days from seven [38]. If this requirement is not met, the accelerometer data will be discarded and not be included in the analysis. The number of participants who fail to record sufficient records of physical activity will be recorded. The accelerometers will be set to record activity over 15-s intervals (epochs), with activity counts of four consecutive epochs summed to give activity counts per minute (cpm). Based on recommendations from previous studies [39], four categories of activity intensity will be defined:

Sedentary behaviour 0–499 cpm.Light intensity activity 500–1,951 cpm.Moderate intensity activity 1,952–5,724 cpm.Vigorous intensity activity greater than 5,725 cpm.

The accelerometer data will then be used to calculate the mean time (minutes) and the percentage time per day, spent in each level of activity.

In addition, physical activity levels will also be measured subjectively by administering the International Physical Activity Questionnaire-Short (IPAQ-S). This will provide information about the types of physical activity they participated in.

### Health-related quality of life

To allow comparison with weight loss studies that do not include adults with intellectual disabilities as participants, the EQ-5D [40] will be used to measure health-related quality of life. The EQ-5D has been shown to be reliable, valid and sensitive to change in adults with obesity [41].

Completion of generic measures, like the EQ-5D, can be difficult for adults with intellectual disabilities because of the levels of communication and abstraction required. The EQ-5D has been used as a proxy-measure of health-related quality of life in studies involving adults with cognitive impairments due to dementia [42, 43] and stroke [44]. In this study, carers will be asked to complete the EQ-5D as a rating of the carer views of the five domains in the EQ-5D, rather than as proxy-rating. Individuals with mild intellectual disabilities will also be asked to complete the EQ-5D and the level of agreement with carer ratings examined. The wording from the youth version of the EQ-5D will be used as it is aimed at young people aged 7 years and older and is appropriate to the of verbal comprehension of adults with mild/moderate intellectual disabilities.

### Process measures

An in-depth process evaluation of the interventions will be conducted as a separate study on completion of the study. Process measures will be collected as part of the treatment protocol, as the research dietitian will also complete written clinical notes at the end of each intervention session, noting the success of components of the interventions, and ways they adapted the approach (in accordance with the manual) to individual need and circumstances. The research dietitian will also collect routine data on the number of sessions attended, participants’ body weight and information about the participants’ dietary habits, physical activity and their success in using the behaviour change techniques. Analysis of process evaluation data will provide insight into multiple aspects of the interventions and will capture experiences gained with delivering the interventions and the fidelity of the interventions which will be used to help inform the development of a full-scale clinical trial.

### Data analysis

The main analysis of the pilot study will include descriptive statistics of feasibility outcomes, including recruitment rates and the acceptability of randomisation (recorded from attrition rates). This analysis will help inform the development of a full-scale trial. Additional analysis of patient-centred outcomes will be carried out according to a detailed pre-specified statistical analysis plan. The primary efficacy analysis, change in body weight at the end of the intervention period (≈12 months) from baseline will use a linear regression (random effects) model to take into account clustering and will be adjusted for randomised group, baseline weight and variables used in the minimisation algorithm (level of intellectual disabilities and presence of Down Syndrome). Similar linear regression models will be fitted for each continuous secondary outcome measure. A logistic regression model will be fitted for the categorical outcome, weight loss of 5% or more of initial body weight taking account of clustering and baseline adjustments listed above. Further analyses may assess the effects of baseline characteristics on outcomes and investigate the evidence for interactions with treatment effects using regression models.

Analyses will be conducted according to the intention to treat (ITT) principle. Per-protocol analyses, including only those participants who engaged with the programme, will also be used to test the sensitivity of the ITT results. Analyses will initially be performed using only those individuals for whom outcome data are available. Participants, who are lost to follow-up, will be assessed to see if they were different at baseline to those included in these analyses. As this is a pilot trial, the level of missing data will be recorded, but no value imputation for outcome variables will be conducted.

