**Conclusions:**

The data from this study will generate pilot data on the acceptability of randomisation, attrition rates and the estimates of patient-centred outcomes of TAKE 5, which will help inform future research and the development of a full-scale randomised clinical trial.

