### Aim

The overall aim of this pilot randomised trial is to examine the feasibility of a full-scale clinical trial of the TAKE 5 multi-component weight management intervention in comparison with a health education control intervention.

The key research questions to determine the feasibility of a full-scale randomised clinical trial are the following:Can adults with intellectual disabilities and obesity be recruited to a randomised study of the TAKE 5 intervention versus a health education control intervention?What attrition rates are observed at 6 and 12 months post-randomisation?Are the patient centred outcome measures acceptable to the participants and can they be measured reliably to detect clinically important changes?What are the sample size requirements for a full-scale clinical trial powered at 90% to determine a clinically important difference in body weight?

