### Recruitment

One aim of the proposed study is to examine recruitment and retention to a randomised trial design and inform recruitment strategies that could be used in the development of a full-scale, multi-centre trial. Therefore, this pilot randomised trial will use a multi-point recruitment strategy, involving primary health care services, specialist intellectual disability services, relevant voluntary organisations and care provider organisations. A record will be kept of the numbers of potential participants, and individuals consenting to participate in the study, identified from each of the recruitment points.

The research team will visit staff working in these settings to explain the study and ask if their organisation would be willing to support recruitment to the study. For those staff willing to support recruitment to the study, a supply of study information packs will be provided, comprising information about the study including an invitation for potential participants to participate. Staff will be invited to distribute these packs to service users who they think would fulfil the study inclusion criteria and potentially be willing to take part. Potential participants, who reply to the invitation to the study by post using the self-addressed envelope provided, will indicate whether they would like to meet the researcher to find out more about the study. The researcher (LH) will then contact participants to arrange a visit, at a convenient location to the participant, to discuss the study. Individuals recruited to the study may live together and/or be supported by the same family or paid carers. These factors could make it difficult to randomise people to the different treatment interventions of the study and lead to some contamination between treatments and clustering of outcomes. Cluster randomisation, stratified by (and therefore analysed with adjustment for) the number of individuals within a randomised cluster, level of intellectual disabilities and presence of Down Syndrome will account for the clustering of outcomes and minimise imbalance between study groups.

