## Discussion

The increase prevalence of obesity and health inequalities in adults with intellectual disabilities is further accentuated by the limited access to evidence-based health care in meeting the equality legislation and addressing the health needs of this population group [45]. The need for research on the management of obesity for adults with intellectual disabilities has been emphasised as a priority for research and an important step towards addressing this issue [12, 13].

This pilot study will examine the feasibility of conducting a full-scale trial. The trial will help provide valuable insight into the feasibility of key issues such as the acceptability of randomisation and the fidelity of the intervention delivery.

Both arms of this trial are active interventions designed to support adults to make healthier lifestyle choices, with particularly focussed on supporting weight loss. This study will compare the two dietary strategies, an individualised EDD with quantitative dietary advice against a health education approach without quantitative dietary advice. Both interventions include support to increase physical activity and incorporate behaviour change techniques. Thus, comparing the two interventions will allow the identification of the essential and any superfluous components of the intervention which will be used to inform the optimal management approach to take forward in designing a full-scale clinical trial to address the obesity epidemic in adults with intellectual disabilities.

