It is recognised that specific challenges are likely to arise when conducting research with adults with intellectual disabilities due to their cognitive and communication needs. In particular, it is noted that recruitment of adults with intellectual disabilities to research studies is challenging and is evident from the small sample sizes reported in previous research [11]. A review by Cleaver et al. [50] reported that ethical procedures which are consistent with this study such as the inability to contact potential participants directly and the procedures of taking consent may lead to poor participation in studies involving adults with intellectual disabilities. This study will assess the feasibility of recruiting and retaining adults with intellectual disabilities to a randomised design of a weight management intervention using a multi-point recruitment strategy which will collect information from recruitment sites such as organisations and services for adults with intellectual disabilities. This will be used to identify potential barriers and facilitators to recruitment which will help inform other controlled trials of weight management interventions and also be influential in informing the development a full-scale multi-centre clinical trial.

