## Conclusion

There is limited access to evidence-based health care for adults with intellectual disabilities. Currently, no published controlled studies of weight management interventions for adults with intellectual disabilities meet clinical obesity recommendations. This pilot randomised trial will examine the acceptability of randomisation and attrition rates and provide pilot data on the estimates of patient-centred outcomes of TAKE 5 compared to the health education control intervention. If this study design is acceptable to adults with intellectual disabilities and shows a significant effect on outcome measures, this protocol can serve as a framework or model on which development of a full-scale clinical trial can be based.

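### Acceptability of randomisation is read from attrition, which is a partial and confounded measure because it is counted only in people who have already accepted randomisation

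*Protocol article*

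**What the plan says.** The Data analysis section defines the pilot's main analysis as descriptive statistics of feasibility outcomes, including "recruitment rates and the acceptability of randomisation (recorded from attrition rates"). The parenthesis fixes the measure. The same section refers only the additional analysis of patient-centred outcomes to a separate statistical analysis plan.

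The Aim section sets the time points for attrition: "What attrition rates are observed at 6 and 12 months post-randomisation". Its first key question is about recruitment: "Can adults with intellectual disabilities and obesity be recruited to a randomised study of the TAKE 5 intervention versus a health education control intervention".

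Elsewhere acceptability stands as an output in its own right. The abstract promises "pilot data on the acceptability of randomisation, attrition rates and the estimates of patient-centred outcomes". The Discussion speaks of the "feasibility of key issues such as the acceptability of randomisation and the fidelity of the intervention delivery". The Conclusion says "This pilot randomised trial will examine the acceptability of randomisation and attrition rates".

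Before randomisation, the Recruitment section provides for counts by recruitment point: "A record will be kept of the numbers of potential participants, and individuals consenting to participate in the study". The Discussion adds, of the information collected from recruitment sites, "This will be used to identify potential barriers and facilitators to recruitment".

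**The concern.** A person who will not be allocated by chance can say so by not replying to the pack, by declining the researcher's visit or by declining consent. None of these people is randomised, so none can be lost to follow-up. Attrition is therefore conditional on the attitude it is meant to measure.

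Those who do drop out over 12 months may leave for reasons unrelated to randomisation. The protocol names some itself: a participant who conceives is excluded (Table 1), the control arm was given a maintenance phase to hold participants for the full period (Control intervention), and drop-out is linked to what the control group is offered (Discussion).

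Two wrong readings are possible. Good retention could be reported as acceptance of randomisation when many people had declined because of it. Poor retention in a demanding programme could be reported as rejection of randomisation. The Conclusion makes acceptability of the design one condition for using this protocol as the model for a full-scale trial, so either error would carry into that decision.

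**Working it through.** **Order of events.** The Procedure section gives consent, then a baseline visit, then randomisation. The Aim section counts attrition after randomisation. The attrition denominator is therefore the randomised group, planned as 66 (33 per arm).

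**The plan's own figure.** The Sample size section allows for 20% attrition and states a 95% confidence interval of no more than ±10% for recruitment and retention rates. For retention, 1.96 × √(0.20 × 0.80 / 66) = 0.0965, or ±9.7 points, so the figure reproduces at the planned attrition. The concern is with what the rate measures, not with its precision.

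**Does attrition respond to refusal of randomisation?** Let r be the share of otherwise willing people who refuse because of randomisation. The protocol gives no value, so r is an assumption, shown over a range. With 66 randomised, the number lost beforehand is 66r/(1 − r). Attrition in the randomised group is held at the planned 20%.

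| Assumed r | Refuse because of randomisation | Attrition |
|---|---|---|
| 0% | 0 | 13/66 |
| 10% | 7 | 13/66 |
| 25% | 22 | 13/66 |
| 50% | 66 | 13/66 |
| 75% | 198 | 13/66 |

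The last column does not move, because refusers never enter it.

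**Does attrition move for other reasons?** Hold r at 0 and let programme burden alone produce attrition of 10% to 30% (assumed). Then 66 × 0.10 ≈ 7 and 66 × 0.30 ≈ 20 people drop out, although nobody objected to randomisation.

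**Can the recruitment counts fill the gap?** Let w be the share of potential participants who would join if there were no randomisation. Observed uptake is U = w(1 − r). Counts of potential and consenting participants give U only. Since w cannot exceed 1, r can lie anywhere from 0 to 1 − U:

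- U = 20% (assumed): r between 0% and 80%
- U = 40% (assumed): r between 0% and 60%
- U = 60% (assumed): r between 0% and 40%

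For example, U = 40% arises from w = 40% with r = 0%, and equally from w = 80% with r = 50% (0.80 × 0.50 = 0.40). Low uptake would be seen, but its cause would not. Separating the two needs reasons for declining.

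**Precision of a consent proportion.** With 66 consenting out of N and p = 66/N, the half-width is 1.96 × p × √((1 − p)/66). At p = 0.40 this is 1.96 × 0.40 × √(0.60/66) = 0.075. The maximum, near p = 2/3, is 1.96 × 0.667 × √(0.333/66) = 0.093. A consent proportion built on 66 consenters is thus within the ±10% that the plan already accepts.

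**The case against.** The strongest reply is that the protocol does not rely on attrition alone to judge recruitment. Its first key question is whether people can be recruited to a randomised study, recruitment rates appear in the same sentence as the disputed parenthesis, counts are kept by recruitment point, and the Discussion promises a look at barriers to recruitment. This stands. A reader might infer that the pilot could miss mass refusal altogether, and the documents do not support that: it would appear as a low recruitment rate. What would be missing is how much of the refusal was due to randomisation.

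A second reply is that objection to the arm received can appear only after allocation, as withdrawal. This also stands. It would be too strong to say that attrition carries no information on acceptability. Early withdrawal by arm carries some, and the fix below keeps it.

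Third, acceptability of randomisation is not named among the four key questions in the Aim section. That is correct; its standing rests on the abstract, the Discussion and the Conclusion.

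Fourth, a journal article may leave the coding of reasons for declining to the full protocol or its forms. Silence on this is therefore not counted as a fault. The finding rests on the measure that the article states.

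**Conclusion.** The point holds in limited form. The Data analysis section assigns acceptability of randomisation to a measure that excludes everyone who refused randomisation and mixes in other causes of drop-out. Taken alone, attrition is a partial and confounded measure of an output that the abstract and the Conclusion name separately from attrition and that the Discussion treats as a key issue. Recruitment rates and counts would reveal poor uptake, but the protocol does not tie them to acceptability and, as described, they cannot identify its cause.

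The size of the error cannot be stated, because the protocol gives no refusal rate. The illustrations rest on assumed refusal shares, uptake and attrition. They show only that attrition does not respond to refusal before randomisation, and that uptake of, say, 40% leaves the share refusing because of randomisation anywhere from 0% to 60%. The sample size and the efficacy analysis are not affected.

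**What to change.** In the Data analysis section, replace the parenthesis that equates acceptability with attrition by two measures:

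1. The proportion consenting to be randomised at each recorded stage: potential participants identified, replied, met the researcher and eligible, consented. The main reason for declining, including unwillingness to be allocated by chance, is recorded where the person volunteers it at the researcher's visit. Reporting every stage matters, because a denominator of people who met the researcher would leave out those who did not reply or declined a visit.
2. Withdrawal between allocation and first session, by arm, with reason. Because the researcher collecting outcomes is blind to allocation, the research dietitian should keep this record.

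Report attrition at 6 and 12 months by arm as retention only.

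**Cost.** About one extra field on the recruitment record already planned, a short entry for early withdrawals, and one changed phrase. No visit and no change in sample size is needed. Reasons will be incomplete, cannot be obtained from people who never reply, and may be missing for refusals before the change, since recruitment began in February 2014. If recruitment has finished, interpret acceptability from the existing consent counts together with early withdrawal by arm, and state that the share of refusals due to randomisation is unknown.
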